### Outcomes

#### Primary Outcome

The primary outcome indicator in this study is the difference in the SCORAD score change from baseline (week 0) to week 4. The SCORAD index is made of the affected body surface area, skin lesion severity, and patient self-assessment of itching and quality of sleep. It is an evaluation method to assess the severity of AD as objectively as possible.

The SCORAD score includes the doctor's assessment (A, B) and the patient's own assessment (C), which is the most comprehensive evaluation method. (A) involves evaluating the affected area, including the head and neck area (accounting for 9%), both upper limbs (accounting for 9% each), both lower limbs (accounting for 18% each), the front and back of the trunk (accounting for 18% each), and the genital area (accounting for 1%). (B) involves 6 clinical features, including erythema, edema or papules, exudation or scabbing, epidermal peeling, lichenification, and dryness. Each feature is scored according to its severity, ranging from 0 to 3 points for each item. The patient self-assessment (C) includes itching and sleep deprivation in the last 3 days. The SCORAD score is calculated as A/5+7×B/2+C, with the total score ranging from 0 to 103 points. A higher score indicates a more severe disease condition. According to the score, the condition is considered mild (0-24 points), moderate (25-50 points), or severe (>50 points) [17]. In this study, the SCORAD will be estimated at baseline (week 0), week 2, week 4, and week 8.

#### Secondary Outcomes

##### Overview

The secondary outcome indicators include the SCORAD score at week 2 and week 8; Peak Pruritus Numerical Rating Scale (PP-NRS), Investigator’s Global Assessment (IGA), Patient-Oriented Eczema Measure (POEM), and Dermatology Life Quality Index (DLQI) at week 2, week 4, and week 8; and the proportion of participants receiving remedial treatment, the amount of levocetirizine tablets used, and the recurrence rate at week 8 [18,19]. A comprehensive study schedule is provided in Table 1, and details of secondary outcome indicators are included.

**Table 1 table1:** Study schedule of the WuSheZhiYang (WSZY) pill clinical trial (8 weeks).

Indicator	Baseline	Treatment		Follow-up
	Visit 1 (week 0)	Visit 2 (week 2)	Visit 3 (week 4)	Visit 4 (week 8)
Informed consent	✓	—^a^	—	—
Demographic feature	✓	—	—	—
History of surgical treatment	✓	—	—	—
History of disease	✓	—	—	—
Vital sign	✓	✓	✓	✓
Physical examination	✓	—	✓	—
Pregnancy examination	✓	—	—	✓
Inclusion/exclusion criteria check	✓	—	—	—
Randomization	✓	—	—	—
SCORAD^b^	✓	✓	✓	✓
PP-NRS^c^	✓	✓	✓	✓
IGA^d^	✓	✓	✓	✓
POEM^e^	✓	✓	✓	✓
DLQI^f^	✓	✓	✓	✓
Proportion of participants receiving remedial treatment	—	—	—	✓
Levocetirizine tablets used	—	—	—	✓
Recurrence rate	—	—	—	✓
Routine blood tests	✓	—	✓	—
Route urine tests	✓	—	✓	—
Blood biochemistry	✓	—	✓	—
Electrocardiogram	✓	—	✓	—
Drug use history	—	✓	✓	—
Concomitant medications	—	✓	✓	✓
Adverse events	—	✓	✓	✓

^a^Not applicable.

^b^SCORAD: Scoring Atopic Dermatitis.

^c^PP-NRS: Peak Pruritus Numerical Rating Scale.

^d^IGA: Investigator’s Global Assessment.

^e^POEM: Patient-Oriented Eczema Measure.

^f^DLQI: Dermatology Life Quality Index.

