### Sample Size

In this study, the sample size was calculated based on the difference in the change in SCORAD score from baseline (week 0) to week 4, as the primary indicator, between the treatment group (urea ointment and WSZY pills) and control group (urea ointment and placebo WSZY pills). Based on previous evidence on the efficacy of TCM for AD treatment, we used a difference of 9.8 (SD 12) points [16]. ‌Sample size estimation‌ was performed using PASS 15.0 software (NCSS Statistical Software). Using the SD of 12.0, the sample size calculation for the 2:1 randomization design indicated that 36 patients with AD in the treatment group and 18 patients with AD in the control group would provide 80% statistical power to detect a difference of 9.8 points in the improvement in the SCORAD score at a 2-tailed α level of .05. Considering a dropout rate of 10%, we plan to enroll 40 patients with AD and 20 patients with AD in the treatment group and control group, respectively.

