### Statistical Analysis

All data will be systematically recorded in the CRF and subsequently entered into a dual-validated electronic database using EpiData software 3.1, with final analyses performed using SAS 9.4. Quantitative variables that are normally distributed will be described using mean and SD, and those a skewed distribution will be described using median and interquartile range. Student *t* tests or Wilcoxon rank-sum tests will be used to compare the differences between groups for quantitative variables as appropriate, depending on the data distribution. Categorical variables will be presented as frequencies and proportions (%), and chi-square tests will be used to compare the differences in categorical variables between the groups. In addition, when the expected frequency is low (<1), Fisher exact tests will be used to compare the differences in categorical variables between the groups. In this study, a 2-tailed α level of .05 will be viewed as statistically significant. Statistical analyses will follow the intention-to-treat principle, including all randomly assigned patients regardless of protocol adherence or study completion [21]. We will handle missing data based on the assumption of missing-at-random and use the sequential regression multiple imputation method, which imputes missing values using regression models for each variable, conditional on the other variables in the data [22]. Additionally, analyses will be performed on both the full analysis set and the per-protocol set.

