Findings in this study are expected to provide several key points for AD treatment. The research results cover the relationship between the administration of WSZY pills and changes in SCORAD, PP-NRS, IGA, POEM, and DLQI scores, as well as the recurrence rate in patients with AD. The aim is to explore the effects of WSZY pills on the severity of AD, itching level, quality of life, and recurrence rate in patients with AD, thereby evaluating their efficacy. Based on these findings, we can recommend an additional treatment option for patients with AD, which will help alleviate their condition, reduce their medical burden, and facilitate long-term treatment and management. In all, this clinical trial will provide additional evidence for the clinical efficacy of WSZY pills for AD treatment and provide a new treatment option for patients with mild-to-moderate AD, which can also alleviate their disease condition and reduce their medical burden. We will share our results through publications covering skin problems, as well as through high-impact, internationally peer-reviewed journals.

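### The scales are compared by unadjusted tests although each is measured at baseline, and SCORAD is a change at week 4 but a score at weeks 2 and 8; a baseline-adjusted model would settle both

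*Protocol article*

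**What the plan says.** The Primary Outcome section defines the endpoint as "the difference in the SCORAD score change from baseline (week 0) to week 4". The Secondary Outcomes overview then states: "The secondary outcome indicators include the SCORAD score at week 2 and week 8". The Abstract makes the same switch.

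The other four scales are listed by instrument and visit only, for example "Dermatology Life Quality Index (DLQI) at week 2, week 4, and week 8". Their own subsections give scoring ranges and assessment times but do not say whether the value or its change is compared. The Discussion (Summary) speaks of "changes in SCORAD, PP-NRS, IGA, POEM, and DLQI scores", with no visits.

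For the comparison itself, the Statistical Analysis section says that Student t or "Wilcoxon rank-sum tests will be used to compare the differences between groups for quantitative variables as appropriate", with the choice depending on the distribution. It names no baseline covariate. Table 1 schedules all five scales at week 0.

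**The concern.** One scale, measured four times in the same patients, is described in two metrics. With an unadjusted test, the estimated group difference on the score and on the change differ by exactly the observed baseline difference between the arms. In a trial of 40 v 20 patients that difference need not be small. The SCORAD results at weeks 2, 4 and 8 would then respond differently to the same chance imbalance, and a p-value could fall on either side of 0.05 according to the metric used.

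The choice matters only because the stated tests ignore baseline. They leave unused a measurement that the trial takes on every patient for every scale, and they give up precision for the primary outcome as well as the secondary ones.

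**Working it through.** **Inputs from the protocol (Sample Size).** Difference 9.8 points and SD 12 for the change ("we used a difference of 9.8 (SD 12) points"); 36 and 18 evaluable patients; 40 and 20 enrolled after 10% dropout; 80% power; two-sided 0.05.

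**Assumed, not in the documents.** The correlation ρ between baseline and visit (0.3 to 0.8), equal variances at the two times for the power figures, and bivariate normal data.

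**1. The plan's own figure.** Control n = (1 + 1/2) × (12/9.8)² × (1.960 + 0.842)² = 17.7, so 18, and 36 on treatment. 36/0.9 = 40 and 18/0.9 = 20. Power at 36 v 18 is 80.8% by the normal approximation and 79.3% by the noncentral t. The stated sample size reproduces.

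**2. What a chance baseline gap does.** Let the arms differ by d at baseline. With equal variances, the expected shift in the estimated difference is:
- score: ρ × d
- change: ρ × d − d = −(1 − ρ) × d
- baseline as covariate: none, if the relation to baseline is linear with a common slope

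For example, a gap of 3 points at ρ = 0.7 moves the score by +2.1 and the change by −0.9. At ρ = 0.5 the shifts are +1.5 and −1.5. Neither metric is free of the gap. Its standard error at 36 v 18 is √(1/36 + 1/18) = 0.29 baseline SDs.

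**3. Precision.** Score SD = 12/√(2(1 − ρ)). Adjusted SD = score SD × √(1 − ρ²). Noncentral t power for 9.8 points at 36 v 18:

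| ρ | Score SD | Adjusted SD | Power, change | Power, score | Power, adjusted |
|---|---|---|---|---|---|
| 0.3 | 10.1 | 9.7 | 79% | 91% | 93% |
| 0.5 | 12.0 | 10.4 | 79% | 79% | 89% |
| 0.7 | 15.5 | 11.1 | 79% | 58% | 85% |
| 0.8 | 19.0 | 11.4 | 79% | 42% | 83% |

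The adjusted column ignores the cost of estimating the slope. Allowing for it (51 degrees of freedom instead of 52, and variance raised by the factor 1 + 1/50) lowers the adjusted powers by less than one percentage point.

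**4. Does the ordering need equal variances?** No. With baseline SD s0, visit SD s1 and a common slope, the adjusted variance is s1²(1 − ρ²). The score variance exceeds it by ρ²s1², and the change variance exceeds it by (s0 − ρs1)². Both excesses are zero or positive, so adjustment is at least as precise as either metric, apart from the small cost noted in step 3.

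**5. How often the two unadjusted tests disagree.** In 20,000 simulated trials per setting (36 v 18), score and change differed on significance in 19%, 23% and 36% of trials at ρ = 0.3, 0.5 and 0.7 with a true difference of 9.8. With no effect they differed in about 8%, and at least one of the two was significant in about 9%, against 5% for a single test.

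**6. After adjustment.** Subtracting baseline from the response of a linear model that already contains baseline changes only the baseline coefficient, by 1. The treatment effect, its standard error and its p-value are identical for score and change.

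**The case against.** The strongest reply is that the metric of a secondary scale is a detail that a journal article may leave to the full protocol or analysis plan. That stands: if the wording were the only issue, there would be no finding. The point rests on the test that the article does state, which is unadjusted.

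Several stronger readings are tempting but not supported:
- A reader might infer that Methods and Discussion contradict each other. The Discussion phrase is narrative, gives no visits and defines no endpoint. A primary change beside secondary scores is an unexplained switch, not a contradiction.
- A reader might infer that all secondary scales are defined as scores, leaving two written definitions to choose between after seeing the data. For PP-NRS, IGA, POEM and DLQI the metric is simply not stated, and a document not shown may fix it.
- A reader might infer that the score carries the whole baseline gap and the change none of it, so that the visits cannot be read together. Step 2 shows that both carry part of it. Both target the same mean difference.

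It is also fair that the planning values belong to the week-4 primary outcome. The eligibility limits on baseline severity make equal variances doubtful, and normal-theory results say little about a 6-point IGA. The power figures are therefore an illustration. The ordering in step 4 does not need equal variances.

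**Conclusion.** The point holds as an improvement to a stated method. Unadjusted comparison leaves the result exposed to chance baseline imbalance and wastes precision on either metric; the SCORAD wording adds an avoidable switch between visits. At the primary outcome's planning values, adjustment takes power from 79% on change to between 93% and 83% for ρ from 0.3 to 0.8, and it is never below the power on the score in that range. These sizes rest on an assumed correlation, equal variances and normality, and cannot be carried over to the secondary scales, for which the documents give no effect, SD or correlation.

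For the secondary outcomes this is minor. Randomisation still protects the unadjusted comparisons from bias on average, and the sample size is correctly derived for the change and need not be altered.

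**What to change.** In Statistical Analysis, replace the unadjusted between-group comparison of SCORAD, PP-NRS, POEM and DLQI at weeks 2, 4 and 8 with a linear model containing treatment and that scale's own baseline value. Include the week-4 primary SCORAD; otherwise an unadjusted week 4 would sit between adjusted weeks 2 and 8. For IGA, use an ordinal model or a rank-based analysis adjusted for baseline, not a linear change.

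In the Abstract and the Secondary Outcomes overview, use one wording for SCORAD at all visits, for example change from baseline, and state the metric for the other scales.

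The cost is a change of wording and model. Table 1 already collects every baseline value, so no data, visits or patients are added. The protocol places the start of analysis in January 2026 and keeps the statistician blinded, so the change should be recorded before unblinding.

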##### PP-NRS

Pruritus severity in patients with mild-to-moderate AD will be quantified using the validated PP-NRS, which is an 11-point patient-reported instrument (0=no pruritus; 10=extreme pruritus). Participants will self-report their maximum itch intensity over the preceding 24 hours using this standardized metric. Scores of PP-NRS will be stratified as 0 (none), 1-3 (mild), 4-6 (moderate), 7-8 (severe), and 9-10 (extremely severe). In this study, the PP-NRS will be evaluated at baseline (week 0), week 2, week 4, and week 8.

##### IGA

The IGA is a rough score based on the doctor's subjective judgment and allows researchers to quickly evaluate the severity of disease. This validated 6-point ordinal scale assesses the following key clinical features: no erythema (0), minimal erythema with barely perceptible edema/papules (1), mild erythema with detectable edema/papules (2), moderate erythema with evident edema/papules (3), severe erythema with marked edema/papules (4), and extreme skin involvement with confluent erythema and edema (5). Longitudinal assessments of the IGA will be implemented at baseline (week 0), week 2, week 4, and week 8.

##### POEM

POEM focuses on the frequency and severity of 7 symptoms (itching, sleep disorders, bleeding, exudation, cracking, scales, and dryness) in the last week through the patient’s own assessment. All items are scored using a 5-point rating system: 0 (none), 1 (mild), 2 (moderate), 3 (severe), and 4 (extremely severe). The total POEM score (range: 0-28) is derived by cumulatively scoring the individual items, with a higher score indicating more severe illness. In this study, POEM will be evaluated at baseline (week 0), week 2, week 4, and week 8.

##### DLQI

The DLQI systematically evaluates impairment of quality of life in the last week across 6 key domains, including physiological response, psychological feeling, family, interpersonal communication, occupational restrictions, social activities, and treatment response [20]. Using a 4-point severity scale (0=none, 1=mild, 2=severe, 3=extremely severe) across 10 relevant items, the total score of the DLQI (range: 0-30) is calculated by summing the 10 items, with a higher DLQI score indicating a lower dermatology quality of life. In this study, the DLQI will be evaluated at baseline (week 0), week 2, week 4, and week 8.

### Data Collection and Management

Standardized data collection will be implemented using a case report form (CRF) completed by trained dermatologists. The CRF includes 6 parts: (1) demographic characteristics, covering age, height, and weight; (2) history of surgical treatment and diseases; (3) vital signs and physical examination, including blood pressure, pulse, height, and body weight; (4) severity indicators of atopic dermatitis (SCORAD, PP-NRS, IGA, POEM, DLQI) at baseline (week 0), week 2, week 4, and week 8; (5) pregnancy examination, routine blood tests, routine urine tests, blood biochemistry, and an electrocardiogram; and (6) drug use history, concomitant medications, and adverse events.

The collected data will be uniformly reviewed, coded, and sampled by professional personnel. The database will be established using Epidata 3.1 software, where input validation procedures (including variable type definitions, value ranges, and skip patterns) will be configured for each variable. All data will be entered using the double data entry method by two independent operators. Consistency checks will be performed on the two generated databases. For any inconsistent variables, the original CRF will be consulted to identify and correct errors in the database until complete consistency is reached between both entries. The finalized database will be converted to a SAS data set. Logical checks and validation will be performed using SAS 9.4 software.

### Statistical Analysis

All data will be systematically recorded in the CRF and subsequently entered into a dual-validated electronic database using EpiData software 3.1, with final analyses performed using SAS 9.4. Quantitative variables that are normally distributed will be described using mean and SD, and those a skewed distribution will be described using median and interquartile range. Student *t* tests or Wilcoxon rank-sum tests will be used to compare the differences between groups for quantitative variables as appropriate, depending on the data distribution. Categorical variables will be presented as frequencies and proportions (%), and chi-square tests will be used to compare the differences in categorical variables between the groups. In addition, when the expected frequency is low (<1), Fisher exact tests will be used to compare the differences in categorical variables between the groups. In this study, a 2-tailed α level of .05 will be viewed as statistically significant. Statistical analyses will follow the intention-to-treat principle, including all randomly assigned patients regardless of protocol adherence or study completion [21]. We will handle missing data based on the assumption of missing-at-random and use the sequential regression multiple imputation method, which imputes missing values using regression models for each variable, conditional on the other variables in the data [22]. Additionally, analyses will be performed on both the full analysis set and the per-protocol set.

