## Methods

### Study Design

This study is a double-blind, randomized, placebo-controlled trial to evaluate the efficacy of WSZY pills for AD treatment. It was designed in line with the SPIRIT (Standard Protocol Items: Recommendations for Interventional Trials) statement [13]. Patients with mild-to-moderate AD will be recruited in inpatient and outpatient departments in Shanghai Skin Disease Hospital from December 2024 through December 2025. In this study, 60 patients with mild-to-moderate AD will be randomly assigned (2:1) to the treatment group (urea ointment and WSZY pills; n=40) or control group (urea ointment and placebo WSZY pills; n=20). All participants in both groups will undergo a 4-week treatment phase followed by a 4-week observational follow-up to evaluate the treatment response and disease progression. The flowchart of this study is shown in Figure 1.

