### Randomization

In this study, patients with AD will be randomly allocated at a 2:1 ratio to either the treatment group or the control group. We will use cluster randomization with combined blocks of 4 and 6 to ensure a balanced group allocation. An independent statistician will construct the computer-generated randomization sequences using SAS software (version 9.4; SAS Institute Inc). To ensure allocation concealment, the generated allocation schedules will be sealed in sequentially numbered, light-resistant envelopes and securely maintained by an independent trial coordinating center.

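### With arms of 40 and 20, Welch's t test is a cheap improvement on the Student t test, because the equal-variance test is not robust to unequal SDs under 2:1 allocation

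*Protocol article*

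**What the plan says.** The Statistical Analysis section of the protocol article says that "Student *t* tests or Wilcoxon rank-sum tests will be used to compare the differences between groups", and that the choice is made "for quantitative variables as appropriate, depending on the data distribution". This rule covers the primary outcome, the SCORAD change from baseline to week 4. It names no unequal-variance version of the t test.

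The Randomization section has patients "randomly allocated at a 2:1 ratio to either the treatment group or the control group". The Sample Size section gives the numbers: "we plan to enroll 40 patients with AD and 20 patients with AD in the treatment group and control group, respectively". The planning assumption there is one spread for both arms: "we used a difference of 9.8 (SD 12) points". No SD is given for either arm separately.

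**The concern.** Taken by its name, the Student test estimates one common variance, and that estimate is weighted towards the larger arm. The variance of the mean difference, however, depends most on the smaller arm. With equal arms the two effects cancel; at 2:1 they do not. If the 20 controls are the more variable group, the standard error is too small, so p values are too small and intervals too narrow. If the 40 treated patients are the more variable group, the standard error is too large and power is lost.

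Unequal SDs of change are plausible here. The Inclusion Criteria cap objective SCORAD at 50 but set no lower limit, and the scale ends at 0, so improvement is bounded by each patient's baseline. If the pills work, a mix of responders and non-responders could widen the treated arm's spread, or compression at the floor could narrow it. The direction cannot be known in advance, which favours a method that is valid in both.

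**Working it through.** **Inputs from the protocol article.** Difference 9.8, SD 12, two-sided alpha .05, 80% power, 2:1, 36 and 18 evaluable, 10% dropout, 40 and 20 enrolled (Sample Size); Student or Wilcoxon test (Statistical Analysis).

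**Assumed.** Arm-specific SDs, because the protocol gives none.

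**Step 1: the plan's own figure.** Control n = (1 + 1/2) × (1.960 + 0.842)² × (12/9.8)² = 1.5 × 7.85 × 1.499 = 17.7, rounded up to 18, so 36 treated. Power at 36/18 is 80.8% by the normal approximation and 79.3% by the noncentral t. Dropout: 36/0.9 = 40 and 18/0.9 = 20. The sample size reproduces and is not in question.

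**Step 2: why 2:1 matters.** Let T be the treated and C the control SD.

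- Variance that Student uses, on average: [(39T² + 19C²)/58] × (1/40 + 1/20)
- True variance of the mean difference: T²/40 + C²/20

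With T = 12 and C = 18, Student uses [(39×144 + 19×324)/58] × 0.075 = 202.97 × 0.075 = 15.2. The truth is 3.6 + 16.2 = 19.8. The standard error is 3.90 where it should be 4.45, a ratio of 0.88.

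With T = 18 and C = 12, Student uses 265.03 × 0.075 = 19.9 and the truth is 8.1 + 7.2 = 15.3. The ratio is 4.46/3.91 = 1.14.

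With equal arms of 30 and SDs 12 and 18, both expressions equal 15.6. The problem comes from the allocation.

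**Step 3: simulation.** Normal, complete data at 40/20, with 400,000 replicates per scenario. Power is for a difference of 9.8.

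| SD treated / control | Error, Student | Error, Welch | Power, Student | Power, Welch |
|---|---|---|---|---|
| 12 / 12 | 5.0% | 5.0% | 83.5% | 82.8% |
| 12 / 13.2 | 5.8% | 5.0% | 80.4% | 77.6% |
| 13.2 / 12 | 4.3% | 5.0% | 79.2% | 80.4% |
| 12 / 15 | 6.9% | 5.1% | 75.3% | 69.3% |
| 15 / 12 | 3.5% | 5.0% | 71.7% | 76.2% |
| 12 / 18 | 8.5% | 5.0% | 67.4% | 56.6% |
| 18 / 12 | 2.7% | 5.0% | 59.1% | 69.1% |

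At 30/30 with SDs 12 and 18, Student's error is 5.1%, as Step 2 predicts. At 36/18 the error rates are nearly the same, and Welch's cost at equal SDs is 79.2% − 78.4% = 0.8 points.

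**Step 4: confidence intervals.** Coverage is one minus the error column. A nominal 95% Student interval covers 100 − 8.5 = 91.5% at 12/18 and 100 − 2.7 = 97.3% at 18/12. This applies whatever the true mean difference.

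**Step 5: the other branch.** The Wilcoxon test at 40/20 (40,000 replicates, normal data) rejects in 6.8% of trials with equal means and SDs 12/18, and in 3.5% with SDs 18/12.

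**The case against.** The strongest reply is that under no effect on any patient, randomization gives both arms the same outcome distribution. The SDs are then equal and Student holds 5% for normal data. This stands. A reader might infer from the table that the trial runs a false-positive risk of 8.5%. The documents do not support that: it would need pills that leave the mean unchanged yet make treated patients less variable than controls. What survives is interval coverage, and power when a real effect comes with a wider spread in the treated arm.

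Second, the SD ratios are assumptions. This also stands. The protocol offers only SD 12, the SCORAD cap limits how far change can spread, and an SD of 18 is a strong departure. At a 10% difference the error is within a point of 5%.

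Third, a condensed article may use Student as a general label for the two-sample t test, and an analysis plan that is not shown may report the unequal-variance result. That is possible, but the literal name is that of the equal-variance test.

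Fourth, one might read the plan as using the t test for every quantitative outcome. It does not: skewed outcomes go to the Wilcoxon test, which has a similar weakness that a change of t test leaves in place.

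Finally, Student has the higher power at 12/18 (67.4% against 56.6%). That excess comes from its inflated 8.5% error rate and is no argument for it.

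**Conclusion.** The point holds as a cheap improvement. The plan contains no wrong figure or contradiction here. For quantitative outcomes sent to the t test, including the primary SCORAD change, the named test is fragile at 40 and 20 patients and Welch's test is not. Over assumed SD ratios up to 1.5, Student's error and CI non-coverage run from 2.7% to 8.5% for a nominal 5%, against about 5% for Welch. The practical gains are correct interval coverage and, with treated SD 18 and control SD 12, about 10 points of power (69.1% against 59.1%). The figures rest on normal, complete data and on SDs that the protocol does not give.

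It would go too far to conclude that the stated alpha of .05 fails in this trial, or that Welch's test removes every consequence of unequal SDs. It restores the error rate and not the planned power: with one SD at 18, Welch's power is 69.1% or 56.6%, both below 80%.

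**What to change.** In the Statistical Analysis section, replace Student t tests with Welch's unequal-variance t test. Name it in advance for the primary comparison, with no preliminary test of variances to choose between versions, and take the 95% CI from the same method. Because the plan uses multiple imputation, compute the Welch estimate and standard error in each imputed data set and pool them. If a baseline-adjusted model is used for the primary outcome, give it robust or group-specific residual variance.

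The change is one or two sentences, affects neither data collection nor sample size, and can be made before analysis begins in January 2026. Its price, if the SDs are truly equal, is 83.5% − 82.8% = 0.7 points of power at 40/20. Outcomes that still go to the Wilcoxon test keep the weakness described above (about 7% and 3.5% at an SD ratio of 1.5), so their p values should be read with that in mind.

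### The primary SCORAD change is compared by an unadjusted t or Wilcoxon test chosen from the data; one prespecified ANCOVA on baseline SCORAD would usually be more precise and would fix the target quantity.

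*Protocol article*

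**What the plan says.** The Primary Outcome section states: "The primary outcome indicator in this study is the difference in the SCORAD score change from baseline (week 0) to week 4". The same section adds that "the SCORAD will be estimated at baseline (week 0), week 2, week 4, and week 8", and Table 1 schedules SCORAD at all four visits, so a baseline value is planned for every patient.

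For between-group comparison of quantitative variables, the Statistical Analysis section names the Student t test and, as the alternative, says: "Wilcoxon rank-sum tests will be used to compare the differences between groups for quantitative variables as appropriate, depending on the data distribution". It gives no covariate, no rule for choosing between the two tests and no separate model for the primary outcome. For missing data it will "use the sequential regression multiple imputation method".

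The Sample Size section works with the unadjusted difference in change: "we used a difference of 9.8 (SD 12) points". It arrives at 36 and 18 evaluable patients for 80% power at a two-sided 5% level, and at 40 and 20 enrolled after 10% dropout.

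**The concern.** Three things follow from the stated test.

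- **Precision.** Subtracting baseline fixes its slope at 1. When the correlation between baseline and week 4 is below 1 and the SDs are similar, that slope is too large and the change score carries avoidable noise. ANCOVA estimates the slope instead.
- **Chance imbalance.** With about 18 controls and no stratification factor named in the Randomization section, the arms can differ at baseline by luck. Part of such a difference carries into the difference in change through regression to the mean.
- **Target quantity.** The trial is sized on a mean difference in points. If the observed distribution leads to the Wilcoxon test, the primary result no longer estimates that mean difference. A rank-sum test also has no standard pooling by Rubin's rules, so that branch fits poorly with the planned multiple imputation. A regression coefficient pools directly.

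At stake are the width of the interval and the clarity of the primary result. The validity of the trial is not.

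**Working it through.** **Inputs from the protocol article.** Difference 9.8, SD 12, 36 versus 18 evaluable, two-sided 5% (Sample Size). The correlation r between baseline and week 4 and the SDs by visit are not given, so they are assumptions here.

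**1. The plan's own figure.** By the normal approximation, control n = (1.960 + 0.842)² × 12² × (1 + 1/2) / 9.8² = 17.7, so 18 control and 36 treated. The SE is 12 × √(1/36 + 1/18) = 3.46, and 9.8/3.46 = 2.83. Power is Φ(2.83 − 1.96) = 80.8%. By the noncentral t with 52 df it is 79.3%. Dropout: 36/0.9 = 40 and 18/0.9 = 20. The stated numbers reproduce.

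**2. ANCOVA at the same 36/18.** Take 12 as the SD of change and let both visits have SD s. Then Var(change) = 2s²(1 − r) = 144 and the ANCOVA residual variance is s²(1 − r²). Their ratio is (1 + r)/2, so the residual SD is 12√((1 + r)/2). Power is by noncentral t with 51 df.

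| Assumed r | Variance ratio | Residual SD | Power |
|---|---|---|---|
| t test on change | 1 | 12.00 | 79.3% |
| 0.3 | 0.65 | 9.67 | 93.1% |
| 0.5 | 0.75 | 10.39 | 89.3% |
| 0.7 | 0.85 | 11.06 | 85.3% |
| 0.9 | 0.95 | 11.70 | 81.3% |

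**3. Where the gain shrinks or grows.** In general the residual SD is 12√(1 − c²), where c is the within-group correlation of baseline with change. At c = 0 power is 79.3%: no gain, and one df lost. If the week-4 SD is 1.3 times the baseline SD (change SD still 12), power is 82.8% at r = 0.5 and 79.6% at r = 0.7. If it is 0.8 times, power is about 95.6% at r = 0.5.

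**4. Baseline imbalance.** The SE of a chance baseline difference is √(1/36 + 1/18) = 0.29 baseline SDs. With equal SDs, an imbalance of D points shifts the expected difference in change by (1 − r)D. For D equal to one SE:

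- r = 0.3: s = 10.1, D = 2.93, shift 2.0 points.
- r = 0.5: s = 12.0, D = 3.46, shift 1.7 points.
- r = 0.7: s = 15.5, D = 4.47, shift 1.3 points.

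The target is 9.8 points.

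**5. Choosing the test from the data.** This was simulated at 36/18 with r = 0.5 and 4,000 runs per setting. The choice was made by a Shapiro-Wilk test in each arm, which is an assumption because the plan gives no rule.

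| Data | t | Wilcoxon | Data-chosen | ANCOVA | Type I error, data-chosen |
|---|---|---|---|---|---|
| Normal | 79.5% | 76.4% | 79.1% | 88.5% | 5.0% |
| Skewed (gamma) | 79.7% | 87.2% | 86.3% | 87.8% | 5.1% |

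**6. Unequal variances.** In 200,000 replicates at 36/18, Student's t had a true size of about 8.6% if the control SD is 1.5 times the treated SD, and about 2.7% in the reverse case. The Welch test stayed near 5%.

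**The case against.** The strongest reply is that nothing here is invalid. Randomisation makes the t test on change unbiased, it matches the sample size calculation, and 36/18 reproduces. That stands.

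A reader might infer more than the document supports in four ways.

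- **That baseline is ignored.** It is not: the outcome is a change from baseline. The point is only that the change is not further adjusted.
- **That adjustment is certain to raise power by a known amount.** The document gives neither r nor the SDs by visit. The gain can be nil, and with skewed data the data-chosen test came within about 1.5 points of ANCOVA (86.3% versus 87.8%).
- **That choosing the test from the data inflates the type I error.** The simulation showed 5.0% and 5.1%.
- **That the Student t test will exceed its nominal size.** That needs a more variable control arm. The Sample Size section gives a single SD of 12, and the reverse case is conservative.

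It may also be said that the model belongs in an analysis plan that is not shown. That would answer silence, but the article states which tests will be used, and the criticism is of that stated choice.

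A last objection concerns the remedy. An unspecified robust standard error can itself inflate size slightly in a sample this small. In simulations of ANCOVA at 36/18 with equal variances and a t reference, HC0 gave about 6%, HC1 5.5% and HC3 just under 5%, while ordinary ANCOVA held about 5.1%. That stands, so the fix must name the estimator.

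**Conclusion.** The point holds as a recommendation on precision and on clarity of the target quantity. It is not a finding of error in the test or in the sample size. With a change SD of 12 and equal SDs at both visits, ANCOVA would lift power from 79% to between 81% and 93% for r from 0.9 down to 0.3. The gain is nil if baseline does not predict change. ANCOVA would also remove the expected shift from a one-SE baseline imbalance, about 1.3 to 2.0 points for r from 0.7 to 0.3. Independently of r, the plan leaves open whether its primary result is a mean difference in SCORAD points or a rank comparison. A single named model closes that.

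**What to change.** Before unblinding, replace the generic test sentence, for the primary outcome, with one prespecified analysis:

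- ANCOVA of week-4 SCORAD (or of the change) on treatment and baseline SCORAD, fitted in each imputed data set and pooled by Rubin's rules. Report the adjusted mean difference with its 95% confidence interval.
- Model-based standard errors or, if protection against unequal variances is wanted, HC3 with a t reference. State which.
- A rank-based test as a prespecified sensitivity analysis only, not as an alternative primary test.
- The same model, each with its own baseline, for the continuous secondary scores: SCORAD at weeks 2 and 8, and PP-NRS, POEM and DLQI at weeks 2, 4 and 8.

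The cost is a change of wording and one degree of freedom. Table 1 already schedules every baseline value needed, so no patients, visits or measurements are added, and the sample size can stay as it is.
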